**Figure 1 FI250281-1:**
[figure not shown]
Abbreviations: PD, Parkinson's disease; HY, Hoehn and Yahr scale; ICF, informed consent form; GVS, galvanic vestibular stimulation.
Flow diagram of the study project.

### Outcomes measures

The primary outcome (
Table 1
) for this research is body balance, measured through the mini-balance evaluation systems test (Mini-BESTest), as well as the activities-specific balance confidence scale (ABC Scale).

**Table 1 TB250281-1:** Assessment tools for people with Parkinson's disease recommended by the European Physiotherapy Guideline for Parkinson's Disease
39

Outcome	Instrument
Body balance	Mini-BESTest
Locomotion	Spatio-temporal gait parameters, NFoG-Q
Postural transfer	M-PAS
Manual dexterity	Nine Holes and Pins Test
Physical capacity	6MWD with Borg 6-20, FTSTS
Confidence in body balance	ABC Scale
Fall risk	Mini-BESTest
Disease severity	UPDRS
Quality of life	PDQ-39
Safety and satisfaction	Questionnaires on adverse effects and satisfaction

Abbreviations: 6MWD, six-minute walk; ABC, activities-specific balance confidence scale; Borg 6-20, Borg scale 6-20; FTSTS, five times sit to stand; M-PAS, modified Parkinson activity scale; Mini-BESTest, mini-balance evaluation systems test; NFoG-Q, new freezing of gait questionnaire; PDQ-39, Parkinson disease questionary-39; UPDRS, unified Parkinson's disease rating scale (part III – motor).

The secondary outcomes were spatio-temporal gait parameters measured using the BTS G-walk (Kinetec) inertial sensor system. Freezing of gait, measured with the new freezing of gait questionnaire. Postural transfer, measured with the timed up and go test and the modified Parkinson activity scale (M-PAS). Manual dexterity, with the nine holes and pins test. Physical capacity, measured with the six-minute walk (6MW) and five times sit to stand tests. Furthermore, risk of falling was measured through the Mini-BESTest, with a cut-off point of 16.
37
Disease severity was measures through part III (motor) of the Unified Parkinson's disease rating scale (UPDRS). Quality of life was analyzed with the Parkinson disease questionary-39 (PDQ-39).
38
Finally, patients' safety and satisfaction will be determined through a new questionnaire, in which adverse events and participants' satisfaction after treatment will be recorded.

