In this context, our principal aim was to analyze the effects of GVS associated with physical-functional exercise on the motor control of PD patients. Our specific objectives were to analyze the effects of this treatment on body balance, gait, postural transfer, manual dexterity, physical capacity, confidence in body balance, risk of falling, and quality of life in patients with PD. Furthermore, we aim to analyze its effects on the safety and satisfaction of patients after treatment, as well as its permanent effects over 1 month.

Our hypotheses are that people with PD undergoing treatment with GVS associated with physical-functional exercise will show better motor control performance than those without GVS (placebo). Furthermore, they will perform better in body balance, gait, postural transfer, manual dexterity, and physical capacity tasks. We also expect an improvement in their quality of life, when compared with the placebo group. We believe GVS associated with physical-functional exercise is safe and satisfactory for PD patients, and that its effects will last approximately 1 month after treatment, with patients maintaining physical-functional exercise.

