The study groups should contain 15 patients each. The sample calculation considered how long each patient followed the protocol (∼ 2 months). We found no previous studies with the same outcomes and intervention protocol.

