### Statistical analysis

Initially, descriptive statistics should be used to analyze the data. To this end, summary measures must be calculated, followed by tables appropriate to the nature and measurement level of the variables involved.

The comparison of groups and moments in time throughout the intervention will be done after the verification with normality tests. If data were normally distributed, the repeat measures analysis of variance (ANOVA) will be used to compare groups (placebo and GVS) over time. If not normally distributed, we will use Freidmans's test for non-parametric data. Furthermore, the ANOVA test will be applied to assess the behavior of the quantitative variables before and after treatment and follow-up between groups, and repeated measures ANOVA will be implemented for effect within groups over consecutive treatment sessions. The significance level adopted for the statistical tests will be 5% (a = 0.05). Analyses and graphs will be done using the Statistical Package Social Sciences (SPSS Inc.) for Windows, version 10.0.

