### Ethical considerations

Before starting any research stage, participants will be fully informed verbally and in writing about all the stages of the research and its importance. They are free to accept or not to participate in the study. All participants must sign an informed consent form (ICF).

Participants will not be charged any fees or bonuses for participating and must be aware of their scientific contribution. The researchers will not disclose participants' data or the images captured on video. The data will be used exclusively for scientific purposes.

This research aims to promote new knowledge for professionals in this field. There will be direct benefits for patients, as they will be assessed and treated by an interdisciplinary team to reduce/remove body imbalance, gait alterations, and the risk of falls.

During the assessment and treatment, patients may experience dizziness, body imbalance, and difficulty walking. However, a researcher will always remain close to each patient to avoid falls and adapt the exercises according to their needs and threshold for dizziness and sensory-cognitive-motor difficulties. There will always be two examiners for the gait assessment.

The risks of GVS are related to its adverse effects: itching and discomfort at the stimulation site, as well as local burning. These can be minimized by thoroughly soaking the sponges to attach the silicone electrodes to the skin behind the ears in the mastoid area.

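### Fifteen treated patients cannot show that GVS is safe, and the timing of adverse-event questions should be fixed at each session

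*Protocol article*

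**What the plan says.** The Introduction makes safety an objective: "we aim to analyze its effects on the safety and satisfaction of patients after treatment". It then states an expectation: "We believe GVS associated with physical-functional exercise is safe and satisfactory for PD patients". No event rate, threshold, margin or comparator goes with it.

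Under Outcomes measures, "safety and satisfaction will be determined through a new questionnaire, in which adverse events and" satisfaction after treatment are recorded. Table 1 lists questionnaires, in the plural, for adverse effects and satisfaction, without a time point.

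Under Ethical considerations, the anticipated effects are local: "The risks of GVS are related to its adverse effects: itching and discomfort at the stimulation site, as well as local burning". Dizziness, imbalance and difficulty walking are listed there too, but as possible consequences of assessment and treatment in general.

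Exposure is ten sessions (Intervention) within 4 to 5 weeks (Procedures). On size, the Sample size calculation says "The study groups should contain 15 patients each", with this basis: "The sample calculation considered how long each patient followed the protocol", about 2 months.

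**The concern.** There are two linked problems.

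The first is what the trial can conclude. A hypothesis that a treatment is safe implies ruling out some level of harm. The article names no level, and the group size was not chosen with one in mind. An uneventful trial of this size could be reported as confirming the hypothesis although it would be compatible with fairly common harms.

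The second is how the data are obtained. Itching, discomfort and burning at the electrode site arise when the current is applied. If patients are asked about them once, at the end of the course, a mild effect at the first session must be remembered for up to 4 to 5 weeks. Any forgetting would make GVS look better tolerated, which is the direction of the stated expectation.

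**Working it through.** **Inputs.** From the document: 15 patients per group, ten sessions, 4 to 5 weeks. The true event risks used below are assumptions, because the document gives none.

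**The plan's own figure.** The 15 per group cannot be reproduced. The Sample size calculation gives no effect size, standard deviation, power, event rate or dropout, and states: "We found no previous studies with the same outcomes and intervention protocol". It is taken as given here.

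**Upper limit with no events.** With 0 of n patients affected, the exact binomial upper limit is 1 − α^(1/n) one-sided and 1 − (α/2)^(1/n) two-sided. For n = 15 and α = 0.05:

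- two-sided: 1 − 0.025^(1/15) = 0.218, or 21.8%
- one-sided: 1 − 0.05^(1/15) = 0.181, or 18.1%

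**Chance of missing a harm altogether.** With per-patient risk p, the chance of no case among 15 is (1 − p)^15.

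| Assumed true risk | Chance of no case | Chance of at least one |
|---|---|---|
| 1% | 86.0% | 14.0% |
| 5% | 46.3% | 53.7% |
| 10% | 20.6% | 79.4% |
| 20% | 3.5% | 96.5% |

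**Treated patients needed to exclude a given risk with zero events** (one-sided 95%): n is ln(0.05)/ln(1 − u), rounded up. For u = 10% this is 29 and for u = 5% it is 59. These thresholds are illustrations.

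**Comparison between arms.** With 15 v 15 and no events on placebo, Fisher's exact test gives p = 0.10 at 4 events on GVS and p = 0.042 at 5. A third of the treated group would have to be affected before a difference from zero reached the 5% level.

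**Timing, from the text.** Three places bear on it:

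- The Introduction ties both safety and satisfaction to the period after treatment and sets this beside persistence over 1 month. There, treatment reads as the whole course.
- Statistical analysis uses before treatment, after treatment and follow-up as time points, and adds the word sessions when it means single sessions.
- The section on the evaluation protocol says that the pre-, post- and follow-up evaluation protocol is available with all the instruments. No recording at sessions is described.

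Together these favour the end of the course, but none states it.

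**Recall loss, illustration only.** If a late questionnaire captured 75% or 50% of affected patients (assumed), the chance of recording at least one case of a 10% event would fall from 79.4% to 1 − 0.925^15 = 68.9% or 1 − 0.95^15 = 53.7%. The document gives nothing from which to choose a capture rate.

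**The case against.** The strongest reply is that late recall is inferred. In the Outcomes sentence, the words placing the record after treatment may govern satisfaction alone, and treatment may mean a session. Table 1 speaks of questionnaires, so adverse events may have their own form. The evaluation protocol with its instruments exists but is not shown, and neither is Figure 1. How often a form is completed is a detail that an article can fairly leave to the full protocol. Patients are also monitored during exercise, with a researcher always close by.

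This stands to the extent that nobody can say from the article that events are under-counted. A reader might infer that late recall will overstate safety; the document does not support this, because single end-of-course collection is not stated and the size of any loss is unknown. That the local effects are brief is likewise an inference. Supervision does not settle the matter, however: the text has the researcher prevent falls and adapt exercises, and does not say that events are written down.

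The second reply is that the safety statement is an expectation in an introduction, with no test, margin or decision rule, and that safety is not the primary outcome. That is correct, and a reader should not infer that the plan contains a formal rule for declaring safety from zero events. But the article sets out the expectation among its hypotheses, and the group size cannot support it whatever the timing of the questionnaire.

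Third, 15 patients are informative about common local effects: one with a 20% risk would appear at least once with 96.5% probability. This is true, and it is why a descriptive aim suits the trial.

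**Conclusion.** The point holds in two parts of different strength.

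The firm part is the safety hypothesis. It rests only on 15 treated patients and exact binomial arithmetic. Zero events would leave risks up to 21.8% (two-sided) or 18.1% (one-sided) unexcluded, and a 5% harm would go unseen in 46% of such trials. Dropout would widen these limits.

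The conditional part is the timing. End-of-course collection is the better-supported reading, not the only one. If it is right, effects at early sessions may be under-counted, and the direction would favour GVS; the size cannot be computed from the document. If the full protocol already records events at each session, this part falls away and the first is unchanged.

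This is a worthwhile, inexpensive improvement. It limits what the trial may say about safety and does not touch the efficacy comparison.

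**What to change.** Complete the adverse-event items at the end of each of the ten sessions and again at follow-up, with the same wording and procedure in both arms. Keep the satisfaction items at the end of the course. If the full protocol already does this, say so in the article.

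Report, by arm, the number of patients with each event and its exact 95% confidence interval. Use the patient as the unit: the 15 × 10 = 150 sessions in an arm are not independent, so session counts should be descriptive only.

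Restate the safety hypothesis as an aim to describe tolerability.

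The cost is about a minute per session, or roughly ten minutes per patient over the course, with no extra patients and no change to treatment. Session-level recording does not narrow the zero-event limit, because the number of treated patients stays at 15. That is why the more modest wording is needed as well.

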### Preintervention, postintervention, and follow-up evaluation protocol

The pre- and post-intervention, as well as follow-up evaluation protocol has been prepared and is available with all the instruments used. The assessment procedures follow the European Physiotherapy Guideline for Parkinson's Disease.
39
The assessment will last 1 to 2 hours.

### Intervention

The stimulation period will include ten sessions of GVS associated with physical-functional exercise according to the American Guideline for the Management of Parkinson's Disease.
40
Patients were monitored by our team during aerobic, postural balance, and gait exercises. These three items are of high-quality evidence and muscular strength of recommendation, according to the American Physical Therapy Guideline for the Management of Parkinson's Disease.
40
The series of exercises will be standardized.

### Physical-functional exercises

Physical-functional exercises will be protocolized. Three blocks will be performed, warm-up, after it will be performed visuo-vestibular exercises and finally, gait training. More specific, patients will be asked to stay in orthostatism posture inside a parallel bar to provide security. Then, they will be asked to perform visual fixation (10 times, 10 s each), smooth pursuit (10 series, 10 trials each), adaptation vestibular exercises with visual fixation during horizontal and vertical head movement (10 series of 10 trials each, in sequence).

Finally, there will be gait training (10 minutes) with anterior, lateral, and posterior gait, as well as walking and moving the head to the sides and up and down with their gaze fixed on a target ahead, and passing through and step.

Each block of exercises should last 10 minutes, leading to a total of 30 minutes of physical-functional exercises.

#### 
*Current and dosimetry of GVS*

Dosimetry will be uniform between patients, using noise-type galvanic vestibular current (stochastic phenomenon), with an intensity of 0.7 mA; frequency 1 of 2 Hz and frequency 2 of 20 Hz. Intensities below 1.0 mA can recruit vestibular hair cells and thus progress the pathway as a whole. Furthermore, these frequencies are related to activity in the muscles of the head, trunk, and lower limbs, as well as to postural oscillation, vestibular system activity. Finally, a 20 second upward ramp and 20 second downward ramp, with a total duration of 30 minutes.
20
27
The effective blinding will be ensured for participants with a brief ramp-up current at the start, without sustained stimulation.

#### 
*Positioning the electrodes for GVS*

The current must be delivered through silicone electrodes (5 × 7 cm) positioned on the mastoids people with PD, keeping the cathode on the right and the anode on the left. However, the current type is not polarized in a single direction. The electrodes are soaked in 0.9% saline solution and fixed to the head using an elastic band.

#### 
*Galvanic vestibular stimulation device*

The device used is the Microestim FOCO Research (NKL) stimulator, purchased specifically for the research, with silicone electrodes, coupling sponges, and cables.

#### 
*Sample size calculation*

The study groups should contain 15 patients each. The sample calculation considered how long each patient followed the protocol (∼ 2 months). We found no previous studies with the same outcomes and intervention protocol.

### Statistical analysis

Initially, descriptive statistics should be used to analyze the data. To this end, summary measures must be calculated, followed by tables appropriate to the nature and measurement level of the variables involved.

The comparison of groups and moments in time throughout the intervention will be done after the verification with normality tests. If data were normally distributed, the repeat measures analysis of variance (ANOVA) will be used to compare groups (placebo and GVS) over time. If not normally distributed, we will use Freidmans's test for non-parametric data. Furthermore, the ANOVA test will be applied to assess the behavior of the quantitative variables before and after treatment and follow-up between groups, and repeated measures ANOVA will be implemented for effect within groups over consecutive treatment sessions. The significance level adopted for the statistical tests will be 5% (a = 0.05). Analyses and graphs will be done using the Statistical Package Social Sciences (SPSS Inc.) for Windows, version 10.0.

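### A normality test on the observed data decides between an ANOVA that compares the arms and Friedman's test, which does not, so the main between-arm analysis is not fixed in advance

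*Protocol article*

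**What the plan says.** Three sentences in the Statistical analysis section of the protocol article bear on this.

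- The gate and its first branch: "The comparison of groups and moments in time throughout the intervention will be done after the verification with normality tests", followed by "If data were normally distributed, the repeat measures analysis of variance (ANOVA) will be used to compare groups (placebo and GVS) over time".
- The second branch: "If not normally distributed, we will use Freidmans's test for non-parametric data".
- A further analysis that carries no normality condition: "the ANOVA test will be applied to assess the behavior of the quantitative variables before and after treatment and follow-up between groups".

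The section sets one significance level, 5%, for its statistical tests. The sample size paragraph gives the group size: "The study groups should contain 15 patients each". Outcomes are measured before treatment, after treatment and at follow-up.

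**The concern.** The condition is placed on the data, which read plainly means the observed scores. ANOVA needs roughly normal residuals. Applied to each outcome in turn, the rule can put different outcomes on different tests, and the choice is made after the outcomes are known.

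The two branches also answer different questions. Repeated-measures ANOVA with a group factor can ask whether the arms change differently. Friedman's test asks whether scores differ between visits and has no term for arm. Both arms receive the exercise programme, so improvement over time in both is plausible without any GVS effect. A significant Friedman result could then be taken as support for GVS when it reflects only the shared gain.

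The unconditional between-group ANOVA does not settle the matter. The section does not say whether it replaces, supplements or overrides the gated comparison, so there are two routes to a between-arm claim and no stated priority.

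**Working it through.** **Inputs from the protocol article.** Two groups (Randomization); 15 patients per group (Sample size calculation); three assessments ("The pre- and post-intervention, as well as follow-up evaluation protocol has been prepared"); 5% level (Statistical analysis). The article gives no effect size, SD or power and no figure for how the gate behaves, so there is no figure of its own to reproduce.

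**Assumptions.** Shapiro-Wilk at 5% as the normality test, which extends the plan's 5% level to the pre-test; correlations between visits from 0 to 0.9; for a score with a ceiling, whole numbers from 0 to 28 with the means and SDs shown. None of these is in the article.

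**1. How often normal data trigger the switch.** There are 2 × 3 = 6 arm-by-visit cells per outcome.

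- Six cells, any failure switches: 1 − 0.95^6 = 0.265 if independent. Simulation with correlated visits gives 22–26%.
- Arms pooled, one test per visit: 1 − 0.95^3 = 0.143. Simulation gives 12.5–15%.
- A single test: about 5%.
- All 90 scores in one test: 5–31%, depending on the correlation.

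**2. Whether the rate depends on the GVS effect (six-cell reading).**

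| Scores | No effect | 0.8 SD | Larger effect |
|---|---|---|---|
| Normal | 25% | 23% | 25% (1.2 SD) |
| 0–28, a setting with mean 20–21, SD 4–5 | 30% | 66% | 81% (1.0 SD) |
| 0–28, mean 17, SD 5, both arms gaining 0.3 SD | 26% | 45% | 78% (1.2 SD) |
| 0–28, mean 19, SD 5, both arms gaining 0.3 SD | 31% | 76% | 97% (1.2 SD) |

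The rate is flat on normal data. It rises with benefit only where scores are pushed against a ceiling, and the size of the rise depends strongly on the assumed mean and SD.

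**3. Whether the gate protects type I error.** Without any pre-test at 15 per arm, the group-by-time ANOVA rejected in 4.1–5.2% of null trials on normal, log-normal and ceilinged data. Baseline-adjusted ANCOVA rejected in 4.9% on normal data and 4.8–5.3% on the bounded score. With at least 3,000 trials per setting, the simulation standard error is at most √(0.05 × 0.95 / 3000) = 0.4 percentage points. The ungated comparison already holds its level.

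**4. What the Friedman branch does.** Suppose both arms gain 0.5 SD and GVS adds nothing. With Friedman's test run over all 30 patients:

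P(significant) ≈ P(switch) × P(Friedman significant) + P(no switch) × P(ANOVA significant)

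- Normal data: 0.244 × 0.875 + 0.756 × 0.045 = 0.214 + 0.034 = 0.248. Direct simulation of the two-stage rule gives 24.7%.
- Mean 21, SD 5, ceiling at 28: 0.782 × 0.867 + 0.218 × 0.051 = 0.678 + 0.011 = 0.689. Direct simulation gives 69%.
- Log-normal data: 88% by simulation.

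A separate simulation, set against ANCOVA, gave 26% on normal data and 52% on ceilinged data, compared with 5–6% for ANCOVA alone.

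Running Friedman's test within each arm does not help. On normal data it was significant in 53.5% of trials in the placebo arm. With two independent arms behaving alike, exactly one would be significant with probability 2 × 0.535 × 0.465 = 0.498.

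**The case against.** The case on the other side has four parts.

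- **The ungated ANOVA sentence.** The section promises a between-group ANOVA whatever the normality tests show. A reader might infer that the gate removes the two-group comparison altogether; this sentence means that is not established. It does not fix the main analysis either, because the two sentences are left unreconciled.
- **The 25% figure needs a rule that the article does not state.** Six cells with any failure switching is one reading; others give about 5% or 12–15%. Which normality test is used and on what unit can properly be left to a full protocol or analysis plan, so its absence is not the fault. The fault is the stated rule that the test's result chooses the analysis.
- **Dependence on the effect.** A reader might infer that the gate fails more often the better GVS works. On normal data it does not. The rise requires a ceiling, and the article gives no maximum, mean or SD for its balance scores.
- **A gate can be useful.** It is tempting to say that the gate protects nothing. With a valid between-arm rank test as the alternative, a simulation at 15 per arm found two-stage type I error of 4.5–5.3%. Power rose from 56% to 73% on strongly skewed log-normal data and from 43% to 50% on t(3) data, and was 75% either way on normal data. Some listed outcomes, such as timed tests, may be skewed. This stands against a blanket claim, but it defends a gate leading to a between-arm rank test. The plan's gate leads to Friedman's test.

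**Conclusion.** The concern holds in a limited form. The plan lets a normality test on observed outcomes choose between a test that compares the arms and one that does not, then adds an unconditional between-group ANOVA without saying which governs. The main between-arm analysis is therefore not fixed in advance.

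The switching rates are conditional: about 25% on normal data under the six-cell reading, and about 30% rising to about 65% at 0.8 SD under the assumed ceiling. They count switches, not wrong conclusions. The more serious harm is the destination. If both arms improve by 0.5 SD, the gated route gives a significant result with no GVS effect in roughly 25–50% of trials, and in more under heavier ceilings or skew. Friedman's test remains valid for change over time; the result misleads only when read as a GVS effect. For the between-arm comparison, the gate buys no type I error control at this sample size.

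This should be changed before outcomes are examined. It is a matter of wording in the analysis plan and does not call the design into question.

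**What to change.** Delete the normality gate and the Friedman branch, and merge what remains with the unconditional ANOVA sentence into one statement. Name one between-arm model for every quantitative outcome, used whatever a normality test shows: for example, ANCOVA of the post-treatment score and of the follow-up score, each adjusted for the baseline score. Check residuals rather than raw scores. Fix one sensitivity analysis in advance, either a re-randomisation p-value for the arm effect or a between-arm rank-based analysis.

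The cost is a few sentences and slightly more analysis work; recruitment, visits and treatment are unaffected. In the simulations, ANCOVA at 15 per arm (correlation 0.7 between visits) kept its level, with power at 0.8 SD of 83% on normal data and 70–81% on the bounded score. The downside is some loss of efficiency on strongly skewed outcomes. A permutation p-value from the same model does not recover that loss; a transformation specified beforehand or the rank-based sensitivity analysis can address it.

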About the GVS method applied, the following varied: intensity, from 0 to 0.7 mA; electrodes placed on the mastoids, or on the mastoid and spinous process of the seventh cervical vertebra, or other placements such as mono or bipolar, and biocathode; and duration of stimulation, from 26 seconds to 3 hours. Furthermore, five articles included people with PD in the “on” phase and one article assessed the “on” and “off” phases. The disease's stages ranged from 1 to 4, following the Hoehn and Yahr scale (HY).

The primary limitations observed in the studies that have evaluated the effect of GVS in people with PD are: low number of participants; heterogeneity in clinical pictures (axial symptoms) and disease staging; low statistical power; heterogeneity of GVS parameters and methodologies; and lack of randomization and clinical trial according to the Consolidated Standards of Reporting Trials (CONSORT) guidelines for nonpharmacological interventions.

Additionally, the studies mentioned above did not analyze the effects of GVS associated with physical-functional exercise.
1
27
34
35
Although it has been described that head positioning can interfere with the postural response when a person is standing. Furthermore, the amplitude and direction of head rotation during GVS varies with its positioning, indicating that head movement and posture adopted during the GVS can interfere in the responses.
27

Therefore, the association of physical-functional exercise with GVS should be investigated in patients with PD, since it can potentiate the effects of the latter on motor control. This study has practical and scientific implications and is relevant due to the gaps highlighted in the literature regarding the use of GVS in people with PD and to deepen the knowledge of how this treatment affects motor control in this population. Additionally, the authors propose an innovative non-drug treatment for PD focused on noninvasive neuromodulation techniques that can influence the motor control centers involved in the pathophysiology of PD and minimize fall episodes.

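### The stated between-group ANOVAs treat the pre-treatment score as a response and never adjust for it, and the term that tests GVS is not named: a free gain in precision, not a bias

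*Protocol article*

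**What the plan says.** The Statistical analysis section of the protocol article names two between-group analyses for quantitative outcomes.

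- Repeated-measures ANOVA: "If data were normally distributed, the repeat measures analysis of variance (ANOVA) will be used to compare groups (placebo and GVS) over time". Friedman's test is the alternative for non-normal data.
- ANOVA by time point: "the ANOVA test will be applied to assess the behavior of the quantitative variables before and after treatment and follow-up between groups".

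The assessments are pre-intervention, post-intervention and follow-up, so the pre-treatment score is one of the responses in both analyses. No covariate, ANCOVA or other baseline-adjusted model appears in the article. The section does not say whether the repeated-measures group main effect, the group-by-time interaction or the ANOVA at a given visit answers the hypothesis that GVS outperforms placebo.

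Outcomes measures gives body balance as primary, measured by the Mini-BESTest together with the ABC Scale. On size, the article says "The study groups should contain 15 patients each" and, by way of basis, "We found no previous studies with the same outcomes and intervention protocol".

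**The concern.** In a randomised trial the expected group difference before treatment is zero. A baseline score helps most as a covariate, where it removes between-patient variance from the later comparison. Used as one more response, it can do one of three things, depending on the term that is read:

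- The group main effect averages the zero difference at baseline with the later differences.
- ANOVA at the post visit leaves the baseline out, and the matching ANOVA before treatment tests a difference that randomisation already sets to zero in expectation.
- The group-by-time interaction uses the baseline much as a change score does, which is inefficient when visits are only weakly or moderately correlated.

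With 30 patients, precision is scarce. If the term is left open, the size of the effect and the chance of detecting it depend on a choice that the text does not make.

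**Working it through.** **Inputs from the article.** 15 per arm; three assessments; significance level 5%, taken as two-sided because sidedness is not stated.

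**Assumptions, since the article gives none of these.** Standardised effect d = 0.8 at post and at follow-up; equal correlation r between any two visits, from 0.3 to 0.8; SD of 1 at each visit; no dropout.

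**The plan's own figure.** The 15 per arm cannot be reproduced, because no effect size, SD or power is stated. As a reference, 80% power for an unadjusted two-group comparison needs d = (1.960 + 0.842) × √(2/15) = 2.802 × 0.365 = 1.02 (normal approximation).

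**Formulas**, with n = 15 per arm:

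1. *Group main effect.* The effect is the mean over the three visits, (0 + 0.8 + 0.8)/3 = 0.53, two thirds of 0.8. The variance per patient is (1 + 2r)/3. t test on 28 df.
2. *ANOVA at post.* Effect 0.8, variance 1, noncentrality 0.8/√(2/15) = 2.19 on 28 df, whatever r is.
3. *Group-by-time interaction.* F on 2 and 56 df, noncentrality (n/2) × S/(1 − r), where S is the sum of squared deviations of the visit effects from their mean. For effects 0, 0.8, 0.8, S = (6/9) × 0.64 = 0.427. At r = 0.7 the noncentrality is 7.5 × 0.427/0.3 = 10.67.
4. *ANCOVA at post.* Effect 0.8, variance (1 − r²) × (1 + 1/26), 27 df. The factor 1 − r² is 0.91/0.75/0.51/0.36 at r = 0.3/0.5/0.7/0.8. At r = 0.7 the noncentrality is 0.8/√(2 × 0.51 × 1.038/15) = 3.01.

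**Power:**

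| Test | Effect estimated | r = 0.3 | r = 0.5 | r = 0.7 | r = 0.8 |
|---|---|---|---|---|---|
| Repeated-measures group main effect | 0.53 | 0.49 | 0.41 | 0.35 | 0.33 |
| ANOVA at post | 0.80 | 0.56 | 0.56 | 0.56 | 0.56 |
| Group-by-time interaction (2 df) | undiluted | 0.45 | 0.59 | 0.82 | 0.95 |
| ANCOVA at post | 0.80 | 0.58 | 0.67 | 0.83 | 0.93 |

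Simulations of 20,000 trials at r = 0.5 and r = 0.7 agree with these figures within 0.5 percentage points. With no true effect and r = 0.7, the simulated type I error was 0.050 to 0.052 for every method.

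**Sensitivity to persistence.** If the follow-up effect halves to 0.4, the main effect becomes (0 + 0.8 + 0.4)/3 = 0.40, half of the post effect. For the interaction, S = 0.16 + 0.16 + 0 = 0.32, so at r = 0.7 the noncentrality is 7.5 × 0.32/0.3 = 8.0 and power is 0.69. ANOVA and ANCOVA at post do not depend on the follow-up effect.

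**The case against.** The strongest reply is that comparing groups over time most naturally means the group-by-time interaction. On that reading nothing is diluted and the baseline is used. At r = 0.7 the interaction matches ANCOVA at post (0.82 against 0.83), and at r = 0.8 it is slightly ahead (0.95 against 0.93). A post-minus-pre contrast between groups would also supply a single effect estimate. All of this stands. It does not settle the matter: the article does not choose the interaction, it states a second, unadjusted analysis beside it, and the parity needs both a high correlation and an effect that persists to follow-up.

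Four stronger readings are tempting, and the article does not support them.

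- A reader might infer that the plan dilutes the GVS effect and wastes the baseline. Dilution holds only for the group main effect, and an unused baseline only for ANOVA at post.
- A reader might quote the 93% power that ANCOVA on the mean of post and follow-up reaches at r = 0.7. That figure mixes adjustment with averaging two visits and assumes full persistence. It falls to 74% if the follow-up effect halves.
- A reader might call chance imbalance a bias. With 15 per arm the standard error of a baseline difference is √(2/15) = 0.37 SD, so imbalances will occur. But the randomised post comparison is unbiased over repeated trials, and its standard error already covers them.
- A reader might cite the Introduction's remark on "heterogeneity in clinical pictures (axial symptoms) and disease staging". It describes limitations of earlier GVS studies. This trial restricts entry to modified Hoehn and Yahr stages 2 to 3.

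It is also fair to say that a condensed article may leave the handling of missed visits to a fuller document, so that is not pressed here. The choice of ANOVA methods is different, because the article states it.

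**Conclusion.** The point holds as one of efficiency and clarity. The stated between-group methods name no baseline covariate and do not identify the test of GVS. Against the stated ANOVA at post, ANCOVA at post has higher power at every correlation examined: a gain of 0.02 at r = 0.3, 0.11 at r = 0.5, 0.27 at r = 0.7 and 0.37 at r = 0.8. Against the interaction it gains at low to moderate correlation (0.58 against 0.45 at r = 0.3; 0.67 against 0.59 at r = 0.5) and is about level at 0.7 to 0.8 if the effect persists. Against the group main effect it gains throughout.

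The sizes rest on the assumed 0.8 SD effect, equal visit correlations and no dropout. For the main effect and the interaction they also rest on full persistence. The direction of the comparison with ANOVA at post depends little on these, because ANCOVA multiplies the error variance by about 1 − r². False-positive error is not affected. This is a free improvement and not a must-fix.

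**What to change.** Replace the two overlapping between-group ANOVAs with one stated analysis.

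- Primary: ANCOVA of post-intervention Mini-BESTest on group and baseline Mini-BESTest, with the same model for the ABC Scale, each with its own baseline.
- Follow-up at 1 month: a mixed model with post and follow-up as responses and with baseline score, group, visit and group by visit as terms.
- Report the adjusted group difference with its 95% confidence interval.
- Drop the between-group test at baseline and describe baseline by arm instead.
- Hoehn and Yahr stage may be added as a covariate. This is optional, and its gain was not calculated here.

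The cost is analysis wording and one degree of freedom (28 to 27), or more if stage is added. No patients, visits or measurements are added. The normality check and the Friedman alternative in the same paragraph would need rewording to fit the new model.
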